| DISEASES   | Systemic Lupus Erythematosus (SLE), rheumatoid arthritis (RA), ankylosing spondylitis (AS), psoriatic arthritis (APs), dermatomyositis / polymyositis (DM/PM), systemic sclerosis (SS), systemic vasculitis, primary Sjögren's syndrome, primary antiphospholipid syndrome (APS)                                                                                                                                                                                                                                                                                                                                                                                                                         |
| BACKGROUND | The COVID-19 pandemic has progressed rapidly around the world, reaching lethality of up to 20% in different regions (Garcia LF, 2020). More serious cases were observed in elderly patients and with comorbidities, particularly in those with chronic cardiovascular or respiratory diseases, diabetes and hypertension (Garcia LF, 2020; Emmi G, 2020). SARS-Cov-2 infection has raised particular concern in patients with autoimmune rheumatic diseases (DRAI) (Garcia LF, 2020; Emmi G, 2020). Due to chronic inflammatory autoimmune dysregulation and the regular use of immunosuppressive drugs (Fernandez-Ruiz R, 2020), these patients were considered to be at high risk of contracting SARS- |

|                    |                                                                                                                                                                                                                                                                                                                                                                                                                                                                                                                                                                                                                                                                                                                                                                                                                                                                                                                                                        |
|--------------------|--------------------------------------------------------------------------------------------------------------------------------------------------------------------------------------------------------------------------------------------------------------------------------------------------------------------------------------------------------------------------------------------------------------------------------------------------------------------------------------------------------------------------------------------------------------------------------------------------------------------------------------------------------------------------------------------------------------------------------------------------------------------------------------------------------------------------------------------------------------------------------------------------------------------------------------------------------|
|                    | 
CoV-2 and potentially having a worse prognosis (Fernandez-Ruiz R, 2020).
 
Vaccine response studies are needed to verify the immunogenicity of the COVID-19 vaccine in immunosuppressed patients with rheumatological diseases. In addition, it is relevant to evaluate the safety of the vaccine in these populations.
                                                                                                                                                                                                                                                                                                                                                                                                                                                                                                                                                                                                                    |
| OUTCOMES    | 
Primary Outcome Measure:
 
 
1. Immunogenicity of CoronaVac in a cohort of ARD patients compared with age- and sex-matched controls without these conditions: 
 
- Seroconversion rate of anti-SARS-Cov-2 IgG antibodies
 
- Presence of <math>\geq 30\%</math> of neutralizing activity of SARS-CoV-2 antibodies
 
 
 
2. Safety of CoronaVac in ARD patients compared with controls without these conditions
 
3. Immunogenicity of CoronaVac in a cohort of ARD patients compared with age- and sex-matched controls without these conditions 6 months after the second vaccine dose.
 
4. Immunogenicity of an additional 4th dose of a mRNA (BNT162b2) heterologous SARS-CoV-2 vaccine in poor/non-responders ARD patients previously vaccinated with 3rd of a SARS-CoV-2 inactivated vaccine.
 
 |
| SAMPLE SIZE | 
 
1. AUTOIMMUNE RHEUMATIC DISEASES (ARD) PATIENTS
 The sample size calculation was based on the previous 15% reduction of seroconversion rate after primo vaccination with the 2009 non-adjuvanted influenza A/H1N1 vaccine in a large cohort of ARD patients. Expecting seroconversion rates of 63% in the ARD patient's cohort and 78% in the control group, considering an alpha error of 5% and power of 80%, in 5 : 1 ratio in order to include more ARD patients, the minimum sample required would
 
                                                                                                                                                                                                                                                                                                                                                                                   |

|                     |                                                                                                                                                                                                                                                                                                                                                                                                                                                                                                                                                                                                                                                                                                                                                                                                                                                                                                                                                                                                                                                                                                                                                                                                                                                                                                                                                                                                                                |
|---------------------|--------------------------------------------------------------------------------------------------------------------------------------------------------------------------------------------------------------------------------------------------------------------------------------------------------------------------------------------------------------------------------------------------------------------------------------------------------------------------------------------------------------------------------------------------------------------------------------------------------------------------------------------------------------------------------------------------------------------------------------------------------------------------------------------------------------------------------------------------------------------------------------------------------------------------------------------------------------------------------------------------------------------------------------------------------------------------------------------------------------------------------------------------------------------------------------------------------------------------------------------------------------------------------------------------------------------------------------------------------------------------------------------------------------------------------|
|                     | 
be 445 ARD patients and 89 healthy subjects, sex-matched and with similar ages. Expecting a higher SC rate of 98% for this vaccine, such sample size had a power greater than 99% to detect a 15% reduction in SC of ARD patients. Due to the peak of pandemics ongoing in Brazil during the vaccination period, we invited more patients and controls, expecting a high incidence of previously infected people and a high rate of infections.
 
A sample was calculated for patients with other rare rheumatological diseases, grouped into five diseases (systemic scleroderma, dermatomyositis/myositis, primary Sjogren's syndrome, systemic vasculitis and primary antiphospholipid antibody syndrome) being followed up in Rheumatology outpatient clinic (HCFMUSP). For the calculation, a seroconversion ratio of <math>p_1 = 50\%</math> is assumed for each disease and <math>p_2 = 74.25\%</math> as the average seroconversion of healthy controls. The sample size for each rare disease was 50, thus 250 being the number of patients with other diseases.
 
2. CONTROL GROUP: 271 healthy controls matched for age and sex will be included according to the need for controls for lupus (<math>n = 74</math>), rheumatoid arthritis (<math>n = 61</math>) and ankylosing spondylitis / psoriatic arthritis (<math>n = 136</math>) will be selected to receive the vaccine at HCFMUSP.
 |
| STUDY DESIGN | The study will be prospective observational in a cohort of patients to be vaccinated and that will be compared independently to the healthy, matched control group by sex and age.                                                                                                                                                                                                                                                                                                                                                                                                                                                                                                                                                                                                                                                                                                                                                                                                                                                                                                                                                                                                                                                                                                                                                                                                                                             |
| POPULATION   | 
Inclusion criteria:
 
 
- RA patients according to the classification criteria of the European league against rheumatism (EULAR) / American College of Rheumatology (ACR) (Aletaha D, 2010).
 
                                                                                                                                                                                                                                                                                                                                                                                                                                                                                                                                                                                                                                                                                                                                                                                                                                                                                                                                                                                                                                                                                                                                                                       |

|  |                                                                                                                                                                                                                                                                                                                                                                                                                                                                                                                                                                                                                                                                                                                                                                                                                                                                                                                                                                                                                                                                                                                                                                                                                                                                                                                                                                                                                                                                                                                                                                                                                                                                                      |
|--|--------------------------------------------------------------------------------------------------------------------------------------------------------------------------------------------------------------------------------------------------------------------------------------------------------------------------------------------------------------------------------------------------------------------------------------------------------------------------------------------------------------------------------------------------------------------------------------------------------------------------------------------------------------------------------------------------------------------------------------------------------------------------------------------------------------------------------------------------------------------------------------------------------------------------------------------------------------------------------------------------------------------------------------------------------------------------------------------------------------------------------------------------------------------------------------------------------------------------------------------------------------------------------------------------------------------------------------------------------------------------------------------------------------------------------------------------------------------------------------------------------------------------------------------------------------------------------------------------------------------------------------------------------------------------------------|

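### The 50 patients per rare disease do not follow from the settings behind the main sample size, and all 271 controls are assigned to other diseases

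*Protocol*

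**What the plan says.** All the figures stand in the Sample Size row of the protocol synopsis.

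- **Pooled comparison.** The rates come from experience with an influenza vaccine: "Expecting seroconversion rates of 63% in the ARD patient's cohort and 78% in the control group". The settings are given as "considering an alpha error of 5% and power of 80%, in 5 : 1 ratio in order to include more ARD patients". The resulting minimum is said to "be 445 ARD patients and 89 healthy subjects, sex-matched and with similar ages". A second scenario follows: "Expecting a higher SC rate of 98% for this vaccine, such sample size had a power greater than 99% to detect a 15% reduction". The row adds that more patients and controls were invited because many prior and new infections were expected.
- **Rare diseases.** For systemic sclerosis, myositis, primary Sjögren's syndrome, systemic vasculitis and primary antiphospholipid syndrome, it assumes 50% seroconversion in each disease and 74.25% in healthy controls. It concludes: "The sample size for each rare disease was 50, thus 250 being the number of patients with other diseases". No alpha, power, sidedness, allocation ratio or control number accompanies this.
- **Controls.** Item 2 of the row says "271 healthy controls matched for age and sex will be included according to the need for controls for lupus" (74), rheumatoid arthritis (61) and ankylosing spondylitis/psoriatic arthritis (136).

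The Study Design row describes one cohort compared with one control group matched by sex and age. The Statistical Analysis row names only unadjusted two-group tests: t or Mann-Whitney, and chi-square or Fisher.

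**The concern.** The rare-disease size is presented as the result of a calculation for each disease, but the reader cannot tell what it was calculated against. The number does not come out of the settings used a few lines earlier, and the control item leaves no control chosen with these diseases in mind.

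Two things are at stake. First, a null result in a disease with 50 patients could be taken as adequately powered when that depends on a control number the protocol does not give. Second, if these 250 patients are compared with the existing controls by the tests named, the comparison is unadjusted and uses controls selected to the needs of other diseases. Their age and sex balance with the rare-disease groups is then unknown.

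Two further gaps make the row hard to use. It does not say whether the 250 lie within the 445 or come on top of them, and it gives no source for 74.25%.

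**Working it through.** **Inputs**, all from the Sample Size row: 63% v 78%, alpha 5%, power 80%, 5:1, 445/89; 98% control rate with a 15% reduction; 50% v 74.25%, 50 per disease, 250 in total; controls 74, 61, 136 and 271. *Assumption:* two-sided testing, which the row does not state.

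**Formula** (two proportions, pooled variance under the null, no continuity correction). With n controls, kn patients and p̄ = (p_c + k·p_t)/(1 + k):

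n = {1.960·√[p̄(1−p̄)(1+1/k)] + 0.842·√[p_c(1−p_c) + p_t(1−p_t)/k]}² / (p_c − p_t)²

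**1. The plan's pooled figure.** p_c = 0.78, p_t = 0.63, k = 5, p̄ = 0.655. The roots are 0.5207 and 0.4671.
n = [(1.960 × 0.5207 + 0.842 × 0.4671)/0.15]² = 88.8, so 89 controls and 5 × 89 = 445 patients. This is an exact match, with power 80.1%. One-sided testing (70/350), a continuity correction (97/485) and unpooled variance (77 controls, about 381 patients) do not match, so this method is very probably the one used.

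**2. The second scenario.** 98% v 83% with 89/445 gives 99.9%, or 99.8% if the 15% is relative (83.3%). The claim of more than 99% holds.

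**3. Pooled comparison with 271 controls.** 445 v 271 at 63% v 78% gives 99.1%.

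**4. Rare diseases by the same method.** p_c = 0.7425, p_t = 0.50, k = 1, p̄ = 0.62125. The roots are 0.6860 and 0.6642.
n = [(1.960 × 0.6860 + 0.842 × 0.6642)/0.2425]² = 61.6, so 62 per group, not 50. Unpooled variance gives 59 and a continuity correction gives 70.

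**5. Power with 50 patients**, two-sided 5%, unadjusted. Power = Φ{[0.2425 − 1.960·s₀]/s₁}, where s₀ and s₁ are the pooled and unpooled standard errors. For 50 v 50, s₀ = 0.0970 and s₁ = 0.0939, so z = 0.557 and power is 71.1%.

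| Controls | Power |
|---|---|
| 50 | 71.1% (Fisher's exact test: 64.4%) |
| 74 | 79.2% |
| 77 | 79.9% |
| 78 | 80.1% |
| 89 | 82.1% |
| 271 | 91.8% |

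**6. What would give about 50.** A one-sided 5% test at 1:1 needs 49 per group (50 v 50 has 81.1%). A two-sided test with 1.5 controls per patient needs 51 patients. Neither setting is stated.

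**7. Sums.** 5 × 50 = 250 and 74 + 61 + 136 = 271 are both right. The second leaves 271 − 271 = 0 controls for the rare diseases. If the 250 lie within the 445, 195 patients remain for all other diseases; if they are additional, the total is 445 + 250 = 695.

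**The case against.** The strongest reply is that the main calculation is sound and the rest is detail. Most of its parts stand.

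- 445/89 is called a minimum and the row says more people were invited, so 271 controls do not contradict 89. They only add power. A reader might infer that the stated sizes and power do not belong to this trial, or that 271 controls at 5:1 would call for 1,355 patients. The protocol does not support either: nothing requires the ratio to be kept above the minimum, and 445/89 fits the pooled comparison in the Outcomes row.
- A reader might count 78%, 98% and 74.25% as three conflicting control rates. The 98% is openly introduced as a second scenario for this vaccine. Only 74.25% is unexplained.
- It would be too strong to say that the rare diseases have no comparator. A healthy-control rate is assumed and the Study Design row offers one common control group. What is missing is the number and allocation.
- The 5% and 80% belong to the pooled calculation. Carrying them over to the rare diseases is an assumption, and 50 is reachable under a one-sided test.

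The reply does not dispose of the point. These are figures that the protocol itself fixes, so they are not matters left to an analysis plan. The explanation for inviting more people does not derive 271, and the stated build-up of 271 goes wholly to three other diseases.

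**Conclusion.** The pooled calculation is correct as a minimum, and the primary comparison is not underpowered. The defect is confined to the rare-disease calculation and the control allocation. Fifty per disease does not reproduce with the method, alpha and power behind 445/89 (62 per group at 1:1). No control is selected or matched for the five diseases, 74.25% has no stated source, and the relation of 250 to 445 is not given.

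Power for each rare disease could be anywhere from about 71% (50 controls) to about 92% (all 271), with 80% reached at 78 controls. A reader might infer that these comparisons are underpowered. That is not shown, because it depends on the unnamed comparator and on unstated settings. The range assumes two-sided 5%, the protocol's 50% v 74.25%, and an unadjusted two-proportion test. Splitting alpha over five diseases (0.01 each) would give 79% against 271, but this is an illustration and not a rule in the protocol.

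This should be fixed; it does not threaten the trial's main conclusion.

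**What to change.** In the Sample Size row:

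1. Give one table of planned patients and controls per disease. State how 89 relates to 271 and whether the 250 are part of the 445.
2. Use one justified control seroconversion rate, or label each rate as a scenario with its source, including 74.25%.
3. Name the comparator for each rare disease, with alpha, sidedness and resulting power: about 71% against 50 controls, 80% with at least 78, about 92% against all 271 (two-sided 5%, unadjusted). The choice of comparator is the sponsor's.
4. If the shared 271 controls are used, adjust the rare-disease comparisons for age and sex, because those controls were selected for other diseases. Say that 92% is an unadjusted approximation.

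The cost is a rewritten row, a recomputed table and an adjusted model for these comparisons. No extra enrolment is needed, provided the sponsor accepts and reports the power that its chosen comparator gives. The stated power for some rare diseases may look less favourable.
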